# PROJECT DESCRIPTION

## GENERAL SITUATION

In Vietnam, over the last ten years, malaria morbidity and mortality have been substantially reduced as a result of an effective national control program (1;2). However, malaria cannot be considered “under control” since the threat of resurgence still exists. Malaria remains endemic in the central highlands, home of ethnic minorities, because of the complex epidemiology of forest malaria. These mountainous and forested areas attract also many migrants from non-endemic provinces and from areas bordering Laos and Cambodia (3;4). Such population movements and specific ecological factors contribute to maintain efficiently malaria transmission and to the re-introduction of malaria parasites where they had disappeared. A recent community-based study in Central Vietnam showed that regular forest activity was a very strong risk factor for malaria infection (5). Untreated bed nets had a significant protective effect for villagers, except for those regularly sleeping in the forest, who suffered a significantly higher number of clinical attacks. This has major economic implications for rural communities as clinical malaria means a substantial number of working days lost and a reduction of the income. Therefore, there is the need of targeting this high-risk group with new interventions based on insecticide-treated material to be tested in field trials (6;7). Hammocks are extensively used by people working in the forest and treating them with insecticide could achieve a good individual protection. In Cambodia, where forest malaria is also common, insecticide-treated hammock nets are used although their impact on malaria morbidity and on the local economy has never been quantified (8). We propose to carry out an extensive evaluation of insecticide-treated hammocks (ITH) targeted to forest workers in order to establish their usefulness for controlling malaria in South-East Asia.

## EXTRA

This is a new project that originates by research carried out in collaboration with Vietnamese colleagues at the National Institute of Malariology, Parasitology and Entomology (NIMPE) in Hanoi, Vietnam, with whom we have established collaboration since 1992 (9-24). Although malaria is being successfully controlled in Vietnam, active foci, mainly in forested areas, continue to maintain transmission. Therefore, the search for an appropriate intervention to deal with this problem is timely and needed.

## PROJECT TITLE: Effectiveness of insecticide-treated hammocks for controlling forest malaria: a community-based trial.

## PROJECT DESCRIPTION

***Overall objective:*** To evaluate the effectiveness of insecticide-treated hammocks (ITH) as a new strategy for malaria control in forested areas of Central Vietnam.

***Specific objectives:***

- To characterise malaria epidemiology and dynamics of transmission in the forested areas of Central Vietnam;
- To measure the effectiveness of ITH in preventing malaria infections among forest workers and other villagers;
- To establish the cost-effectiveness of ITH and their impact on the local economy.
- To increase research capabilities by training a young Vietnamese scientist at PhD level.

***Milestones:*** *DECEMBER 2003*: complete census of study villages, updated yearly for the following 2 years; *FEBRUARY 2004*: Passive case detection of malaria cases set up and running until December 2006; *JUNE 2004*: Health economic study started, first results available by December 2006; *DECEMBER 2004*: Intervention (ITH) is implemented in half of the study villages; *JUNE 2005*: Dynamics of malaria transmission known; *DECEMBER 2006*: 7 malariometric surveys (2 per year) completed and results available; Insecticide-treated hammock distributed to control villages if a significant difference in the intervention villages is found; *JUNE 2007*: publication first results and information to health authorities; *DECEMBER 2007*: completion PhD by a Vietnamese researcher.

***Planned methodology****:*Community-based, cluster-randomised trial in which half of the study villages will received ITH after a first year of baseline data collection. Twenty villages of about 1000 inhabitants situated in a forested area in Binh Thuan province will be identified. Sample size calculated on the basis that the cluster unit is the village and that the intervention will reduce malaria morbidity (malaria antibodies, clinical attacks) in intervention villages by at least 30% (5% level and 90% power). This takes into account the (estimated) coefficient of variation of true proportions between communities and the cluster effect. **Baseline year**: complete census of the study population to be used to randomly select, for each village, a cohort of 50 regular forest workers and of 150 villagers. A Knowledge, Attitudes and Practices study (forest activities, hammock use and basic economic indicators) and 2 malariometric surveys (one at the beginning and one at the end of the transmission season) to collect baseline information and allow stratification of the villages according to key variables (for example malaria prevalence and seropositivity, acces to treatment, etc.) and their randomisation into 2 groups within each stratum. Passive detection of clinical cases (collection of blood slides and treatment) set up and running between surveys. Quarterly entomological collections (human landing catches) within and around 2 study villages for species identification and Entomological Inoculation Rate calculation (EIR). **Intervention** (2 years): ITH distributed to all adults (age>15 years) in the 10 intervention villages. Bi-annual malariometric surveys and passive detection of clinical cases continued in all villages. Evolution of malaria antibodies prevalence and incidence of clinical malaria among the cohorts under surveillance determined and compared between intervention and control villages. Direct and indirect costs linked to malaria clinical attacks will be determined and the cost involved in preventing a clinical case will be calculated.

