## PROJECT OPERATIONS

**Start**: November 2003, **Phases/stages**: One year baseline data collection; randomisation villages in 2 groups and distribution of ITH in the intervention villages at the end of the baseline year; Insecticide re-treatment of ITH every year for 2 years; Continued surveillance malaria morbidity for 2 years; Health economic study during the intervention years; Data analysis and result publications; discussion with Vietnamese authorities on scaling up if intervention successful. **Measures**: Coverage and compliance of ITH in study villages; incidence of infection (malaria antibodies) and clinical attacks (passive surveillance) and comparison between intervention and control villages; direct and indirect costs linked to clinical malaria; cost of preventing a clinical attack with ITH; EIR, vector species and their behaviour. **Deadlines**: see Milestones. **End**: Field activities ended by December 2006; Data analysis and reports/publications by June 2007; PhD completion by December 2007. **Implementation**: ITM is responsible for the overall co-ordination and management of the project; NIMPE, Hanoi, is responsible for the local implementation and management of the project; the provincial malaria station in Binh Thuan is responsible for the implementation of the ITH at village level and for the local co-ordination and supervision of field activities.

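### The serological outcome is antibody prevalence in one place and incidence of infection in another; comparing prevalence dilutes an effect on infection, by an amount that depends on antibody persistence

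*Protocol*

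**What the plan says.** The Planned methodology paragraph states the comparison for the two intervention years: "Evolution of malaria antibodies prevalence and incidence of clinical malaria among the cohorts under surveillance determined and compared between intervention and control villages". The antibody part is a prevalence, followed over time in the cohorts. The Measures list under Project operations describes the antibody outcome as "incidence of infection (malaria antibodies) and clinical attacks (passive surveillance) and comparison between intervention and control villages". The relevant specific objective is "To measure the effectiveness of ITH in preventing malaria infections among forest workers and other villagers".

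The sample size rests on one effect for both outcomes, namely that "the intervention will reduce malaria morbidity (malaria antibodies, clinical attacks) in intervention villages by at least 30% (5% level and 90% power"), and refers to variation in true proportions between communities. Each village contributes "a cohort of 50 regular forest workers and of 150 villagers", chosen in the baseline year, before any hammock is distributed. Nothing in the protocol restricts the antibody comparison to people seronegative at the start of the intervention or to new seroconversions.

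**The concern.** Prevalence counts everyone who carries antibodies at a survey. Incidence counts new infections over a period. The protocol attaches both names to one measure, so whoever writes the analysis cannot tell which is meant, and the paragraph that sets the comparison names the one further from the objective.

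The difference matters because the area is endemic and villages are to be stratified on baseline seropositivity, so some cohort members are expected to be positive before the intervention. A hammock cannot undo a past infection. Until those antibodies wane, such members count as positive in both arms and the contrast in prevalence lags behind the contrast in infection. At stake is a missed effect. The Milestones make distribution to control villages conditional on a significant result, and Project operations ties scaling up to success.

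**Working it through.** **Inputs in the protocol.** 10 villages per arm ("ITH distributed to all adults (age>15 years) in the 10 intervention villages"); 50 + 150 = 200 cohort members per village; 30% reduction, 5% level, 90% power; two years of intervention.

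**Inputs not in the protocol, assumed here.** Starting seroprevalence P0 of 20–30%; half-life of seropositivity from 3 months to 5 years; between-village coefficient of variation k = 0.15 (the protocol says only "This takes into account the (estimated) coefficient of variation of true proportions between communities and the cluster effect"); a two-sided test.

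**1. The plan's own figure.** For proportions with m = 200 per village, the villages needed per arm are

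c = 1 + (1.96 + 1.28)² × [p0(1−p0)/m + p1(1−p1)/m + k²(p0² + p1²)] / (p0 − p1)².

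With p1 = 0.7·p0, c = 10 is reached when k is about 0.14, 0.17, 0.19 or 0.21 at p0 = 15%, 20%, 30% or 40%. At p0 = 10% it is not reached even with k = 0. The stated size therefore cannot be reproduced exactly, but it is compatible with a 30% fall in prevalence itself. With k = 0.15 and p0 = 0.30, the variance term is 0.00105 + 0.00083 + 0.00302 = 0.00490, and power = Φ(√(9 × 0.09²/0.00490) − 1.96) = Φ(1.90) = 97%. At p0 = 0.20 it is 93%.

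**2. What a 30% cut in infection does to prevalence.** In a reversible catalytic model starting at equilibrium, ρ = ln 2 / half-life and λ = P0·ρ/(1 − P0). With infection at 0.7λ, P* = 0.7λ/(0.7λ + ρ) and P(t) = P* + (P0 − P*)·exp(−(0.7λ + ρ)t).

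Example, P0 = 0.30 and half-life 2 years: ρ = 0.347, λ = 0.149, P* = 0.231, and P(2) = 0.231 + 0.069 × exp(−0.901) = 0.259, a relative fall of 13.7%.

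| Half-life | P(2), P0 = 20% | Fall | P(2), P0 = 30% | Fall |
|---|---|---|---|---|
| 3 months | 0.149 | 25.5% | 0.231 | 23.1% |
| 1 year | 0.159 | 20.5% | 0.242 | 19.3% |
| 2 years | 0.172 | 14.2% | 0.259 | 13.7% |
| 5 years | 0.186 | 7.1% | 0.279 | 7.0% |

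The 3-month row has already reached the new equilibrium. Its shortfall from 30% arises because prevalence is not proportional to the infection rate. The further shortfall in the lower rows is carry-over of antibodies acquired before distribution.

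**3. Power for that effect, k = 0.15.** For one end survey, P0 = 0.30 and half-life 2 years: variance term 0.00554; Φ(√(9 × 0.0411²/0.00554) − 1.96) = Φ(−0.30) = 38%. The two right-hand columns come from simulating the same model with the same persons at baseline and year 2, analysed by village with baseline seroprevalence as covariate.

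| Half-life | Prevalence, one end survey | Prevalence, baseline-adjusted | Seroconversion, baseline-adjusted |
|---|---|---|---|
| 1 year | 62–66% | 79–90% | 94–97% |
| 2 years | 34–38% | 59–74% | 81–90% |
| 5 years | 11–13% | 30–42% | 50–64% |

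The seroconversion column is idealised, because it counts every conversion.

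**4. The reverse reading.** If the 30% means a fall in prevalence by two years, infection must fall by 43–45% (half-life 1 year) or 62–63% (2 years). Stopping all infection lowers prevalence by 1 − 2^(−2/h), where h is the half-life in years. This is below 30% once h exceeds 2·ln 2/ln(1/0.7) = 3.9 years.

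**5. Seroconversion as the measure.** Among people seronegative at the previous survey six months before, a 30% cut in infection shows as a 25–30% reduction (half-life 0.5–5 years, P0 10–40%).

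**The case against.** The strongest reply is that the plan compares the evolution of prevalence in cohorts surveyed before the intervention, after randomisation stratified on seropositivity. The single-survey powers therefore do not describe it. This stands, and the baseline-adjusted column is the fairer one. It still falls short of seroconversion under the same adjustment.

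The advantage of seroconversion should not be overstated. Variation of 0.15 in prevalence implies about 0.15/(1 − P0) in the infection rate, that is 0.19 at 20% and 0.21 at 30%. Without baseline adjustment, seroconversion then has 83–86%, 74–76% and 50–57% power at 1, 2 and 5 years. At 1 year and 30% seroprevalence, adjusted prevalence does better (about 89% against 83%). The adjustment is therefore part of the remedy.

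A reader might infer four stronger things that the protocol does not support:

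- **That serology is the only comparison.** Clinical incidence stands beside it, without carry-over, and the cost analysis rests on clinical cases.
- **That one arm is favoured.** Randomisation balances carry-over; the effect is diluted in both directions of inference only towards no difference.
- **That the observed effect must be much smaller.** With a 3-month half-life most of it remains.
- **That the 30% cannot apply to antibodies.** It can be read as a fall in prevalence; step 4 shows what that reading demands.

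The risk set for seroconversion could be left to a statistical analysis plan, and repeated cohort surveys allow it. But the protocol itself names two different quantities, and that conflict needs settling there.

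**Conclusion.** The point holds in limited form. The Planned methodology paragraph and Project operations name different serological quantities, and the one set for comparison is not the one the objective calls for. Followed as written, the prevalence comparison dilutes an effect on infection in every scenario examined. The dilution is modest if antibodies last a few months, about a third at a half-life of 1 year, and half or more from 2 years on. These sizes, and the powers in step 3, are conditional on half-life, seroprevalence and k, none of which the protocol gives, and on a model starting at equilibrium. Seroconversion is closer to the objective and has more power under equal adjustment, but it does not guarantee 90% when antibodies persist for years and new conversions are few.

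**What to change.** Use one term for the antibody outcome in Planned methodology and Project operations. Define the serological comparison as seroconversion among cohort members seronegative at the last survey before ITH distribution, as a village-level rate per person-year at risk, adjusted for village baseline seroprevalence. Keep antibody prevalence, also adjusted for baseline, as a secondary measure. State that the 30% in the sample size applies to the infection (seroconversion) rate. A survey carried out after distribution should not be relabelled as baseline; the protocol does not date individual surveys, so the dividing line should be the distribution itself.

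The cost is in wording and analysis only, since the cohort, surveys and sera are unchanged. The downsides are small: seropositive members leave the denominator, results must be linked by person across rounds, conversions that revert between six-monthly surveys are missed, and readings near the assay cut-off add noise.

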## PROJECT OPERATIONS

**Start**: November 2003, **Phases/stages**: One year baseline data collection; randomisation villages in 2 groups and distribution of ITH in the intervention villages at the end of the baseline year; Insecticide re-treatment of ITH every year for 2 years; Continued surveillance malaria morbidity for 2 years; Health economic study during the intervention years; Data analysis and result publications; discussion with Vietnamese authorities on scaling up if intervention successful. **Measures**: Coverage and compliance of ITH in study villages; incidence of infection (malaria antibodies) and clinical attacks (passive surveillance) and comparison between intervention and control villages; direct and indirect costs linked to clinical malaria; cost of preventing a clinical attack with ITH; EIR, vector species and their behaviour. **Deadlines**: see Milestones. **End**: Field activities ended by December 2006; Data analysis and reports/publications by June 2007; PhD completion by December 2007. **Implementation**: ITM is responsible for the overall co-ordination and management of the project; NIMPE, Hanoi, is responsible for the local implementation and management of the project; the provincial malaria station in Binh Thuan is responsible for the implementation of the ITH at village level and for the local co-ordination and supervision of field activities.

## LEVERAGE

# The project will improve our knowledge on the dynamics of malaria transmission in forested area and consequently key determinants to be targeted by control activities will be identified.

- The project will evaluate a new intervention for preventing forest malaria, a major problem for south-eastern Asian countries, and, if successful, it could change the approach to malaria control in this region.
- Large-scale implementation of ITH could increase the quality of life of people living in remote places, usually local minorities, by reducing the burden of malaria and consequently improving the local economy.
- The project will further consolidate the scientific collaboration between ITM and NIMPE whose competitiveness for international grants will increase.

## 2.7 INCLUSION OF AND DELEGATION OF TASKS: see section 2.5, Implementation.

## 2.8 EXIT OR HAND OVER SCENARIO: This project will be included into the long-term institutional collaboration between ITM and NIMPE for which an agreement exists until 2007. Such collaboration is funded by the Belgian co-operation and it is usually renewed every 5 years. Therefore, this proposal fits perfectly into this framework, as the collaboration between the 2 institutions will continue even after the completion of the proposed study.

# 2.9 COMPETITION: To our knowledge this type of research question has never been explored in Vietnam and no other research groups are currently working on it.

# PROJECT MANAGEMENT

- ***Scientific management*:** [name] and [name] will co-ordinate all aspects of the project in collaboration with colleagues at NIMPE. Communication and discussion of the results will be done at yearly meeting. The co-ordination will be assisted by a local full time project assistant taking care for the day-to-day activities in Vietnam.

### *Administrative management:* ITM-Antwerp has a long practice in administration of externally funded projects. General management will be performed by a professional administrator of ITM-Antwerp, who will interact with administrative responsible of NIMPE and provide administrative reports to the co-ordinator.

- ***Evaluation:*** The institutional collaboration project between ITM and NIMPE has been recently evaluated by external auditors. The project was evaluated extremely well (see joint document)

**TIMETABLE**

| **ACTIVITIES** | **YEAR 1** | | | | YEAR 2 | | | | **YEAR 3** | | | | **YEAR 4** | | | |
| --- | --- | --- | --- | --- | --- | --- | --- | --- | --- | --- | --- | --- | --- | --- | --- | --- |
| **Quarters** | **1** | **2** | **3** | **4** | **1** | **2** | **3** | **4** | **1** | **2** | **3** | **4** | **1** | **2** | **3** | **4** |
| Preparation, Training |  |  |  |  |  |  |  |  |  |  |  |  |  |  |  |  |
| Census |  |  |  |  |  |  |  |  |  |  |  |  |  |  |  |  |
| KAP survey |  |  |  |  |  |  |  |  |  |  |  |  |  |  |  |  |
| Entomological surveys |  |  |  |  |  |  |  |  |  |  |  |  |  |  |  |  |
| Health economic study |  |  |  |  |  |  |  |  |  |  |  |  |  |  |  |  |
| Intervention (ITH) |  |  |  |  |  |  |  |  |  |  |  |  |  |  |  |  |
| Cross-sectional surveys |  |  |  |  |  |  |  |  |  |  |  |  |  |  |  |  |
| Passive case detection |  |  |  |  |  |  |  |  |  |  |  |  |  |  |  |  |
| Laboratory work |  |  |  |  |  |  |  |  |  |  |  |  |  |  |  |  |
| Supervision |  |  |  |  |  |  |  |  |  |  |  |  |  |  |  |  |
| Data entry, cleaning |  |  |  |  |  |  |  |  |  |  |  |  |  |  |  |  |
| Data analysis, |  |  |  |  |  |  |  |  |  |  |  |  |  |  |  |  |
| Discussion results, |  |  |  |  |  |  |  |  |  |  |  |  |  |  |  |  |
| PhD training |  |  |  |  |  |  |  |  |  |  |  |  |  |  |  |  |
| Report/paper writing |  |  |  |  |  |  |  |  |  |  |  |  |  |  |  |  |
| Information to health authorities |  |  |  |  |  |  |  |  |  |  |  |  |  |  |  |  |

